#### Secondary outcomes

The following secondary outcomes will be assessed:
Gestation at booking;Booking before 25 weeks;Measures of size: crown to heel length, head circumference;Measures of stage: gestational age at delivery, weight-for-dates (standardised; SGA babies are those weighted less than the 5th centile weight, or LGA weighted more than the 90th centile weight), term at birth (preterm, babies are born at less than 37 weeks gestation; term babies are those born between 37 and 42 weeks gestation and post-term babies are born after 42 weeks gestation);Birth outcomes: mode of delivery, stillbirths, neonatal deaths, 5 min Apgar score. Although there is some debate concerning the robustness of the Apgar score as an outcome, it is in common use and we will therefore present results for this outcome within the context of the wide debate on the subject.

Due in part to the introduction of smoking ban in Scotland in 2006, an additional outcome of interest is maternal smoking. Maternal smoking is collected at booking and during pregnancy. The health advice given when receiving the HiP grant might have an impact on smoking rates during pregnancy over and above that of the smoke-free legislation. We will analyse the temporal change in smoking rate by socioeconomic class and its effect on outcomes.

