### Sample size

The data are clustered in small areas, 6505 data zones. The sample size calculation takes this clustering into account. Assuming an average of 56 000 singleton live births per year, and allowing for the clustering within the 6505 data zones in Scotland (average population 780/data zone) with an estimated intraclass correlation coefficient of 0.05, we have power of 0.90 to detect an effect of 7 g change in birth weight at a 95% significance level. This is not to say that 7 g is a clinically important threshold; rather, it is indicative of the power of the study. The large national data set available to us will allow for subgroup analysis. In the 20% most deprived areas, we will have power of 0.80 to detect an effect of 13 g; among the 26% of single mothers, we will have power of 0.80 to detect an effect of 11 g. To put these small effects into context, 50 g is the estimated mean birth weight reduction reported in the meta-analysis of the effect of interventions in pregnancy on maternal and obstetric outcomes.^27^

We anticipate item non-response for some outcomes and explanatory variables. Our primary outcome measure, birth weight, has a completion rate of 99.9%. There is high completion rate (<1.5% missing) for all obstetric variables,^46^ with the exception of crown to heel length (15% missing) and head circumference (12% missing). The item non-response ranges from 8% for maternal smoking to 20% for marital status. We will use multiple imputation to account for missing data and all analyses will compare the results of analyses of complete cases and multiple imputation.^63^ Imputed models will be constructed such that they contain as many relevant predictor variables as possible. The more variables that are used the greater the amount of information available on which estimations are made. We will use all (or as many as possible) obstetric and maternal variables in an imputation model to predict the missing values. It is difficult to identify in advance the number of multiple imputed data sets we will need to construct but it is likely to be between 5 and 10. We will then analyse these data sets identically and combine the results to get the estimates and SEs for the multiple imputed data. These results will be compared with the complete case analysis results.

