### Data analysis plan

#### Statistical analysis

Descriptive statistics of all variables will be presented as mean, SD, minimum, median and maximum for continuous variables and as proportions when the variables are categorical.

The main statistical design we will use is interrupted time series.^64^ Segmented regression analysis will allow an estimation of the size of the effect of the HiP grant at different time points, as well as changes in the trend of the effect over time after its implementation.

Outcomes will be measured on individual births, which are nested within mothers, with mothers themselves clustered within data zones and Health Boards. Multilevel univariable and multivariable models will be used to determine whether the outcomes changed during the period in which the HiP grants were in effect. Multilevel linear regression will be used when the outcome is continuous and multilevel binomial logistic regression when the outcome is dichotomous. Multilevel multinomial logistic regression will be used for the multicategory outcomes mode of delivery and 5 min Apgar score.

All analyses will be adjusted for temporal trends and seasonal variations in outcomes in addition to maternal age, sex of child, parity, marital status, height, weight at booking, diabetes, smoking status, gestation at booking, maternal diabetes, social class, maternal smoking and area deprivation.

The effect of HiP grant on birth weight might have a carryover effect after the withdrawal of the grant. In other words, postintervention the slope in birth weight might not fall back to the same rate as preintervention. This could be due to women who have gave birth during the intervention subsequently having a birth postintervention but still heeding the health advice given during their first pregnancy. We will carry out an additional analysis only on primiparous women to avoid such contamination.

We will analyse preterm births stratified by mode of delivery and stratified according to whether the birth was induced or spontaneous.

We will repeat the main analyses including (ie, adjusting for the effect of) ethnicity along with other covariates and compare the results with analyses excluding ethnicity to gauge the impact of this on our results. We note that the quality of this variable (including the completeness of recording) is poorer than for other variables and that only 1–2% of mothers delivering in Scotland are from minority ethnic backgrounds.

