^66^ According to Rothman,^65^ reducing the type I error for null associations increases the type II error for those associations that are not null. He recommends a policy of not making adjustments for multiple comparisons because it will lead to fewer errors of interpretation when the data under evaluation are not random numbers but actual observations on nature.

The HiP grant was introduced and withdrawn at the same time as other interventions that may have an impact on birth weight. Healthy Start is a means tested voucher scheme for pregnant women. If they are in receipt of certain benefits or under 18 years old, then they are eligible for free vitamins and vouchers to be spent on fruits and vegetables. This scheme replaced the means tested parts of the Welfare Food Scheme in the UK (including Scotland in 2006) and is still currently in place. During this period, there were policy changes in the optimal timing of first booking appointments due to changes in blood tests offered to pregnant women in the Pregnancy Screening Programme. These changes were first discussed in 2008 and had to be implemented by all Health Boards by March 2011.^67^
^68^ Early booking is a HEAT target of the Scottish Government (Health improvement for the people of Scotland, Efficiency and governance improvements, Access to services, Treatment appropriate to individuals H11.1).^69^ At least 80% of pregnant women in each SIMD quintile will have booked for antenatal care by the 12th week of gestation by March 2015.

A further piece of legislation that may affect birth weight is the introduction of the smoking ban in public places in Scotland in March 2006. Mackay *et al*^70^ reported a reduction in the prevalence of current smoking among women who conceived after the introduction of the legislation prohibiting smoking. They also reported a reduction in small and very SGA, as well as in absolute LBW after the legislation. We will carry out a further analysis restricting the preintervention HiP grant period to April 2006 to March 2009.

It is possible that harm may have occurred due to the cash transfer. The £190 was given to pregnant women with no restriction as to how it should be spent, and we do not know how the money was used. We are examining how the intervention group differed; birth weight could have reduced or increased. We will carry out two-sided hypothesis tests to ensure that we are able to detect any such potential harmful effect.

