D. Environmental and behavioural risks												
Income domain of the SIMD	Χ	Χ	Χ	Χ	Χ	Χ	Χ	Χ	Χ	Χ	Χ	Χ
Urban/rural status of the area of residence	Χ	Χ	Χ	Χ	Χ	Χ	Χ	Χ	Χ	Χ	Χ	Χ
Booking status (gestational age at booking, booking before 25 weeks)	Χ			Χ	Χ	Χ	Χ	Χ	Χ	Χ	Χ	Χ
Smoking status (before and during this pregnancy)	Χ	Χ	Χ	Χ	Χ	Χ	Χ	Χ	Χ	Χ	Χ	
Typical weekly alcohol consumption (before and during this pregnancy)	Χ	Χ	Χ	Χ	Χ	Χ	Χ	Χ	Χ	Χ	Χ	Χ
Drug misuse during this pregnancy	Χ	Χ	Χ	Χ	Χ	Χ	Χ	Χ	Χ	Χ	Χ	Χ
*II. Unmeasured covariates*												
Maternal weight gain												
Maternal nutrition												
Maternal education												
Maternal exposure to stress												
Maternal physical activity												
Exposure to toxic substances												
Birth interval												
History of preterm birth												
Statistical methods												
Multilevel linear regression	Χ	Χ		Χ			Χ					
Multilevel binomial logistic regression			Χ			Χ			Χ		Χ	Χ
Multilevel multinomial logistic regression					Χ			Χ		Χ		

Χ: variables which will be considered for adjustment in the statistical analysis.

SIMD, Scottish Index of Multiple Deprivation.

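### Weight-for-dates is planned only as logistic regression after a centile cut; a linear model of the standardised score should be reported beside the SGA and LGA models

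*Protocol article*

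**What the plan says.** The Secondary outcomes section places weight-for-dates among the measures of stage and describes it as follows: "weight-for-dates (standardised; SGA babies are those weighted less than the 5th centile weight, or LGA weighted more than the 90th centile weight". It is thus called standardised, but what is spelled out is two cuts, which form three groups: SGA, neither, and LGA.

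The Statistical analysis section gives the rule for choosing a model: "Multilevel linear regression will be used when the outcome is continuous and multilevel binomial logistic regression when the outcome is dichotomous". Multinomial models are for outcomes with several categories.

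In the statistical methods rows at the foot of Table 2, the weight-for-dates column is marked in one row only, "Multilevel binomial logistic regression". The linear row is marked for birth weight, gestation at booking, gestational age at delivery and the two size measures. The multinomial row is marked for term at birth, mode of delivery and Apgar score.

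Table 2 lists gestational age at delivery and sex for the birth weight model, but its footnote says only that marked variables will be considered for adjustment. The Statistical analysis section has a separate list of variables for which all analyses will be adjusted. That list has sex of the child and gestation at booking, but not gestational age at delivery.

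**The concern.** Size for gestation separates better fetal growth from longer gestation. Growth is the part of birth weight closest to the nutrition pathway that the article gives as a reason for choosing birth weight as primary outcome. If size for gestation is analysed only through the tails, a small general shift in growth is easily missed, and a null SGA or LGA result could be read as no effect on growth.

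The choice also departs from the plan's own pattern. Gestation at booking is cut (booking before 25 weeks) and also kept on its full scale with a linear model. Gestational age at delivery is cut (term at birth) and also kept on its full scale. Weight-for-dates has no full-scale model under its own name. In addition, a single binomial mark does not show how three groups are to be handled, whereas term at birth, also with three groups, is marked multinomial.

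**Working it through.** **The plan's own figure.** The Sample size section states "we have power of 0.90 to detect an effect of" 7 g in birth weight, "at a 95% significance level", with an intraclass correlation of 0.05 and 6505 data zones; tests are two-sided (Statistical analysis). No standard deviation is given, so the figure cannot be strictly reproduced. With assumptions it can be approached:

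- Births at 56 000 per year: intervention period, 25 months, 116 667; pre plus post, 63 + 32 = 95 months, 443 333.
- Assumed SD 550 g.
- Design effect from one year's births per data zone: 1 + (56 000/6505 − 1) × 0.05 = 1.38.
- Detectable change at power 0.90: 550 × √1.38 × √(1/116 667 + 1/443 333) × (1.960 + 1.282) = 6.9 g. Power for 7 g is 0.91, which agrees with the stated 0.90.
- With no design effect the power is 0.97. With a design effect from all years' births per data zone (5.25) it is 0.39.

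The figure depends on these choices, but the comparison below does not. It is a ratio, so the SD cancels, and so does the design effect if it is the same for both analyses.

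**Efficiency of a cut.** For a normal score with a small uniform shift, a binary analysis at centile p keeps the fraction φ(z_p)² / [p(1 − p)] of the full-scale information.

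- SGA, p = 0.05, z = −1.645, φ = 0.1031: 0.01064 / 0.0475 = 0.224.
- LGA, upper tail 0.10, z = 1.282, φ = 0.1755: 0.0308 / 0.09 = 0.342.

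**Power where the full scale has 0.90.** Power = Φ(√efficiency × (1.960 + 1.282) − 1.960).

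- SGA: Φ(0.473 × 3.242 − 1.960) = Φ(−0.43) = 0.335.
- LGA: Φ(0.585 × 3.242 − 1.960) = Φ(−0.06) = 0.475.

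Where the full scale has 0.80, the same formula with 0.842 in place of 1.282 gives 0.26 and 0.37.

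**Growth in the detectable shift.** 1/√0.224 = 2.1 for SGA and 1/√0.342 = 1.7 for LGA.

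**Check with actual proportions.** A 7 g shift was applied with assumed SDs of 450 to 550 g, at the sample size that gives power 0.90 on the full scale, with equal groups and with the 25:95-month split. SGA falls from 5.00% to 4.84–4.87% and LGA rises from 10.00% to 10.23–10.28%. Power is 0.33 for SGA and 0.48 for LGA, in line with the formula.

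**Three ordered groups.** If SGA, neither and LGA were analysed together as ordered categories, efficiency would be 0.53 and power about 0.65. This is better than either cut alone and still well short of 0.90.

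**Larger shifts.** Scaling the stated 7 g gives detectable shifts of 7/0.473 = 14.8 g (SGA) and 7/0.585 = 12.0 g (LGA). Both lie well below the 50 g that the Sample size section offers as context, and at 50 g the power of either cut is essentially 1.

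**The case against.** The strongest reply is that a full-scale analysis of nearly the same information is already in view. Birth weight is modelled linearly, and Table 2 lists gestational age at delivery and sex as candidate covariates. Crown to heel length and head circumference are also modelled linearly with gestational age listed. The adjustment list in the Statistical analysis section is not exhaustive, since it also omits urban or rural status, which the Study variables section says will be adjusted for. A null SGA or LGA result would be read beside these models.

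Much of this stands, and it limits the practical loss. It does not remove it: Table 2 says only that the covariate will be considered, and the list that applies to all analyses leaves it out. No analysis that estimates size for gestation on its full scale is firmly committed to.

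Three further replies also stand in part.

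- A reader might infer that the plan breaks its own rule that "Multilevel linear regression will be used when the outcome is continuous". The text does not go that far. That the score is continuous is inferred from the word standardised, which could also mean that babies are classified against a gestation-specific standard. SGA and LGA taken singly are dichotomous, so logistic regression fits the rule for each.
- A reader might infer that 0.34 and 0.47 are the study's power for this outcome, or that the stated 0.90 is wrong. Neither follows. The 0.90 is for birth weight, no power is stated for weight-for-dates, and the article says that 7 g is not put forward as a clinically important threshold.
- The tails matter in their own right. The article warns that a gain in birth weight may not benefit a baby already at risk of being LGA. A mean score can hide opposite movements in the two tails, so replacing or demoting SGA and LGA would not be justified.

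**Conclusion.** The point holds as a loss of precision in one secondary outcome. Weight-for-dates is described as standardised but is planned only as a binary outcome after a centile cut. Under a roughly normal score, a uniform shift, and SGA and LGA prevalences of 5% and 10%, the cuts keep 22% and 34% of the information; power of 0.90 on the full scale becomes about 0.34 and 0.47, and the detectable shift grows about 2.1-fold and 1.7-fold.

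The loss matters for shifts of a few grams, the size that the article uses to indicate its power. The article also allows for differential effects between subgroups. An effect concentrated in one tail would lose less than these figures show, or could be detected better by the cut than by the mean. The documents support adding a full-scale estimate; they do not support calling the SGA and LGA models wrong.

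**What to change.** In Table 2, also mark multilevel linear regression for weight-for-dates, and report the standardised score (standardised for gestation and sex) alongside the SGA and LGA logistic models. SGA and LGA keep their standing, because the tails answer the question of benefit and harm. State that SGA and LGA are two separate binary contrasts, so that the binomial mark and the three groups agree.

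The cost is one more reported estimate for a secondary outcome, partly overlapping with birth weight adjusted for gestational age. No new data are needed.

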### Sample size

The data are clustered in small areas, 6505 data zones. The sample size calculation takes this clustering into account. Assuming an average of 56 000 singleton live births per year, and allowing for the clustering within the 6505 data zones in Scotland (average population 780/data zone) with an estimated intraclass correlation coefficient of 0.05, we have power of 0.90 to detect an effect of 7 g change in birth weight at a 95% significance level. This is not to say that 7 g is a clinically important threshold; rather, it is indicative of the power of the study. The large national data set available to us will allow for subgroup analysis. In the 20% most deprived areas, we will have power of 0.80 to detect an effect of 13 g; among the 26% of single mothers, we will have power of 0.80 to detect an effect of 11 g. To put these small effects into context, 50 g is the estimated mean birth weight reduction reported in the meta-analysis of the effect of interventions in pregnancy on maternal and obstetric outcomes.^27^

We anticipate item non-response for some outcomes and explanatory variables. Our primary outcome measure, birth weight, has a completion rate of 99.9%. There is high completion rate (<1.5% missing) for all obstetric variables,^46^ with the exception of crown to heel length (15% missing) and head circumference (12% missing). The item non-response ranges from 8% for maternal smoking to 20% for marital status. We will use multiple imputation to account for missing data and all analyses will compare the results of analyses of complete cases and multiple imputation.^63^ Imputed models will be constructed such that they contain as many relevant predictor variables as possible. The more variables that are used the greater the amount of information available on which estimations are made. We will use all (or as many as possible) obstetric and maternal variables in an imputation model to predict the missing values. It is difficult to identify in advance the number of multiple imputed data sets we will need to construct but it is likely to be between 5 and 10. We will then analyse these data sets identically and combine the results to get the estimates and SEs for the multiple imputed data. These results will be compared with the complete case analysis results.

It is difficult to be specific about the missing data mechanism until we see the data but much is likely to be missing completely at random (MCAR, eg, certain hospitals are less likely to collect specific items) or missing at random (MAR, when the missingness is related to known variables and, conditional on these, is assumed to be unrelated to unmeasured variables).

### Data analysis plan

#### Statistical analysis

Descriptive statistics of all variables will be presented as mean, SD, minimum, median and maximum for continuous variables and as proportions when the variables are categorical.

The main statistical design we will use is interrupted time series.^64^ Segmented regression analysis will allow an estimation of the size of the effect of the HiP grant at different time points, as well as changes in the trend of the effect over time after its implementation.

Outcomes will be measured on individual births, which are nested within mothers, with mothers themselves clustered within data zones and Health Boards. Multilevel univariable and multivariable models will be used to determine whether the outcomes changed during the period in which the HiP grants were in effect. Multilevel linear regression will be used when the outcome is continuous and multilevel binomial logistic regression when the outcome is dichotomous. Multilevel multinomial logistic regression will be used for the multicategory outcomes mode of delivery and 5 min Apgar score.

All analyses will be adjusted for temporal trends and seasonal variations in outcomes in addition to maternal age, sex of child, parity, marital status, height, weight at booking, diabetes, smoking status, gestation at booking, maternal diabetes, social class, maternal smoking and area deprivation.

The effect of HiP grant on birth weight might have a carryover effect after the withdrawal of the grant. In other words, postintervention the slope in birth weight might not fall back to the same rate as preintervention. This could be due to women who have gave birth during the intervention subsequently having a birth postintervention but still heeding the health advice given during their first pregnancy. We will carry out an additional analysis only on primiparous women to avoid such contamination.

We will analyse preterm births stratified by mode of delivery and stratified according to whether the birth was induced or spontaneous.

We will repeat the main analyses including (ie, adjusting for the effect of) ethnicity along with other covariates and compare the results with analyses excluding ethnicity to gauge the impact of this on our results. We note that the quality of this variable (including the completeness of recording) is poorer than for other variables and that only 1–2% of mothers delivering in Scotland are from minority ethnic backgrounds.

The simplest model for the intervention effect will include a dummy variable ‘intervention’ covering the period from the introduction to the withdrawal of HiP grants, with adjustment for relevant factors such as marital status. (More complex models of the effect of the intervention will include an interaction of the intervention with the temporal trend.) Before carrying out specific subgroup analysis, we will identify differential effects by fitting interaction terms. An assessment as to whether there is a differential effect of the intervention for single women, for example, will involve a test of the significance of the intervention between marital status and the intervention effect. If the interaction is significant this will aid our understanding of the generalisability to other populations, including the rest of the UK. Subgroup analyses will be conducted for those groups seen as having the greatest potential to benefit from the payments such as those living in the most deprived areas, those in the lowest social classes, lone mothers, primiparous women, teen mothers, mothers from ethnic minorities and selected combinations of these groups. For each group we will replicate the main analysis. This reduction in sample size for subgroup analyses will result in fewer women/births being available but the same number of areas (data zones) will be analysed (apart from analyses restricted to those living in the most deprived areas).

An increase in birth weight, although desirable at a population level, may not be a beneficial outcome if the baby were already at risk of being LGA. Separate subgroup analyses will therefore be conducted for women seen to be at high risk of delivering a LGA baby (women with diabetes) and for the remainder of the population. Given that some subgroups may contain small numbers, and bearing in mind the potential importance of the intervention, we will report the results of all subgroup analyses and not just those that reach statistical significance to avoid false negatives. The above process will involve conducting many tests, which will not be independent of each other. Rather than adjusting CIs or p values to account for this we will present the results of all analyses and caution the user regarding the interpretation of the results. Indeed, some statisticians recommend never correcting for multiple comparisons while analysing data.^65^
^66^ According to Rothman,^65^ reducing the type I error for null associations increases the type II error for those associations that are not null. He recommends a policy of not making adjustments for multiple comparisons because it will lead to fewer errors of interpretation when the data under evaluation are not random numbers but actual observations on nature.

The HiP grant was introduced and withdrawn at the same time as other interventions that may have an impact on birth weight. Healthy Start is a means tested voucher scheme for pregnant women. If they are in receipt of certain benefits or under 18 years old, then they are eligible for free vitamins and vouchers to be spent on fruits and vegetables. This scheme replaced the means tested parts of the Welfare Food Scheme in the UK (including Scotland in 2006) and is still currently in place. During this period, there were policy changes in the optimal timing of first booking appointments due to changes in blood tests offered to pregnant women in the Pregnancy Screening Programme. These changes were first discussed in 2008 and had to be implemented by all Health Boards by March 2011.^67^
^68^ Early booking is a HEAT target of the Scottish Government (Health improvement for the people of Scotland, Efficiency and governance improvements, Access to services, Treatment appropriate to individuals H11.1).^69^ At least 80% of pregnant women in each SIMD quintile will have booked for antenatal care by the 12th week of gestation by March 2015.

A further piece of legislation that may affect birth weight is the introduction of the smoking ban in public places in Scotland in March 2006. Mackay *et al*^70^ reported a reduction in the prevalence of current smoking among women who conceived after the introduction of the legislation prohibiting smoking. They also reported a reduction in small and very SGA, as well as in absolute LBW after the legislation. We will carry out a further analysis restricting the preintervention HiP grant period to April 2006 to March 2009.

It is possible that harm may have occurred due to the cash transfer. The £190 was given to pregnant women with no restriction as to how it should be spent, and we do not know how the money was used. We are examining how the intervention group differed; birth weight could have reduced or increased. We will carry out two-sided hypothesis tests to ensure that we are able to detect any such potential harmful effect.

We will conduct sensitivity analyses to increase the probability that any observed effect can be attributed to the HiP grant. The timing of the HiP grant is well-defined and fixed, therefore using the interrupted time-series approach any effects within that window can be observed. We plan to carry out three analyses for this.
We will extend this window for some months before April 2009 (births before the HiP grant was introduced).We will extend this window for some months after April 2011 (births after the HiP grant was withdrawn).We will extend the window both before and after the HiP grant period. In each case we would expect to see a dilution of any effects of the HiP grant.

The statistical analysis plan detailing the outcomes and the covariates, which will be considered for adjustment in the statistical models are presented in table 2.

**Table 2 BMJOPEN2014006547TB2:** Analysis plan detailing the outcomes and the covariates that will be considered for adjustment in the statistical models

	Primary outcome	Secondary outcomes										
	Birth weight	Booking status		Measures of stage			Measures of size:	Other birth outcomes				Maternal smoking during this pregnancy
		Gestation at booking	Booking before 25 weeks	Gestational age at delivery	Term at birth	Weight-for-dates	Head circumference,	Mode of delivery	Stillbirth	5 min Apgar score	Neonatal death	
Covariates							Crown to heel length					
*I. Measured covariates*												
A. Sociodemographic determinants												
A-1. Related to the baby												
Date of birth	Χ	Χ	Χ	Χ	Χ	Χ	Χ	Χ	Χ	Χ	Χ	Χ
Sex	Χ			Χ	Χ	Χ	Χ	Χ	Χ	Χ	Χ	
Gestational age at delivery	Χ						Χ	Χ	Χ	Χ	Χ	
Birth weight							Χ			Χ	Χ	
Mode of delivery										Χ	Χ	
A-2. Related to the mother												
Hip grant	Χ	Χ	Χ	Χ	Χ	Χ	Χ	Χ	Χ	Χ	Χ	Χ
Age	Χ	Χ	Χ	Χ	Χ	Χ	Χ	Χ	Χ	Χ	Χ	Χ
Weight at booking	Χ	Χ	Χ	Χ	Χ	Χ	Χ	Χ	Χ	Χ	Χ	
Height	Χ			Χ	Χ	Χ	Χ	Χ	Χ	Χ	Χ	
Ethnic group	Χ	Χ	Χ	Χ	Χ	Χ	Χ	Χ	Χ	Χ	Χ	Χ
Parity	Χ	Χ	Χ	Χ	Χ	Χ	Χ	Χ	Χ	Χ	Χ	Χ
Marital status	Χ	Χ	Χ	Χ	Χ	Χ	Χ	Χ	Χ	Χ	Χ	Χ
Social class	Χ	Χ	Χ	Χ	Χ	Χ	Χ	Χ	Χ	Χ	Χ	Χ
B. Medical risks of the current pregnancy and before pregnancy												
Diabetes	Χ	Χ	Χ	Χ	Χ	Χ	Χ	Χ	Χ	Χ	Χ	
Hypertension	Χ	Χ	Χ	Χ	Χ	Χ	Χ	Χ	Χ	Χ	Χ	
Infection	Χ			Χ	Χ	Χ	Χ	Χ	Χ	Χ	Χ	
Congenital anomalies	Χ			Χ	Χ	Χ	Χ	Χ	Χ	Χ	Χ	
Induction of labour									Χ	Χ	Χ	
Duration of labour									Χ	Χ	Χ	
C. Medical risks related to previous pregnancies												
Previous spontaneous abortions		Χ	Χ						Χ			
Previous stillbirths		Χ	Χ						Χ			
Previous neonatal deaths		Χ	Χ								Χ	
D. Environmental and behavioural risks												
Income domain of the SIMD	Χ	Χ	Χ	Χ	Χ	Χ	Χ	Χ	Χ	Χ	Χ	Χ
Urban/rural status of the area of residence	Χ	Χ	Χ	Χ	Χ	Χ	Χ	Χ	Χ	Χ	Χ	Χ
Booking status (gestational age at booking, booking before 25 weeks)	Χ			Χ	Χ	Χ	Χ	Χ	Χ	Χ	Χ	Χ
Smoking status (before and during this pregnancy)	Χ	Χ	Χ	Χ	Χ	Χ	Χ	Χ	Χ	Χ	Χ	
Typical weekly alcohol consumption (before and during this pregnancy)	Χ	Χ	Χ	Χ	Χ	Χ	Χ	Χ	Χ	Χ	Χ	Χ
Drug misuse during this pregnancy	Χ	Χ	Χ	Χ	Χ	Χ	Χ	Χ	Χ	Χ	Χ	Χ
*II. Unmeasured covariates*												
Maternal weight gain												
Maternal nutrition												
Maternal education												
Maternal exposure to stress												
Maternal physical activity												
Exposure to toxic substances												
Birth interval												
History of preterm birth												
Statistical methods												
Multilevel linear regression	Χ	Χ		Χ			Χ					
Multilevel binomial logistic regression			Χ			Χ			Χ		Χ	Χ
Multilevel multinomial logistic regression					Χ			Χ		Χ		

Χ: variables which will be considered for adjustment in the statistical analysis.

SIMD, Scottish Index of Multiple Deprivation.

